**F1 (1 month after implantation ± 14 days)**

- Follow-up date
- Current antiarrhythmic medication
- Pacemaker parameters (sensing and pacing thresholds, impedance of the leads etc)
- Keeping records of AF-burden-, mode-switch-, frequency- and sensor histogram, inclusive all stored IEGMs, and deleting the pacemaker storage afterwards
- Analysing of the mode-switch IEGMs in terms of inappropriate mode-switch episodes. In case of inappropriate mode-switch episodes a participant has reached the primary endpoint. The patient will undergo an individual optimisation of the PVAB according to the far-field sensing test results and stay in the study group until the end of the trial
- Programming of the pacemaker according to the study guidelines
- Any hospital stays since discharge, reason for hospitalisation
- Adverse events

**F2 (3 months after implantation ± 14 days = end of trial)**

- Follow-up date
- Current antiarrhythmic medication
- Pacemaker parameters (sensing and pacing thresholds, impedance of the leads etc)
- Keeping records of AF-burden-, mode-switch-, frequency- and sensor histogram, inclusive all stored IEGMs, and deleting the pacemaker storage afterwards
- Analysing of the mode-switch IEGMs in terms of inappropriate mode-switch episodes. In case of inappropriate mode-switch episodes a participant has reached the primary endpoint. The patient will undergo an individual optimisation of the PVAB according to the far-field sensing test results.
- Final programming of the pacemaker
- Any hospital stays since discharge, reason for hospitalisation
- Adverse events

##### 5.4.3.2 Completed Follow-Up period

After completing the F2-follow-up visit (3 months  14 after implantation) of the last participant the trial will end.

Beside the scheduled end of the follow-up there are possibly dropouts ahead of schedule due to withdrawal of the informed consent, changeover to another pacemaker follow-up centre, death of the patient. In all cases there will be a documentation of the dropout-reasons by filling in the from „early end of study“. The following data will be recorded:

- Date of last follow-up
- Reasoning for dropping out

#### 5.4.4 Events / Adverse events

There will be a documentation of every event including date and detailed description on the „event“-form. Furthermore every event has to be classified according to its degree of severity.

- In case of adverse events the sponsor has to be informed within one working day after occurrence
- Additionally in case of serious events the responsible ethics committee and the principal investigator has to be informed directly

#### 5.4.5 Far-field Sensing Test

Only patients within the control group and those of the study group with inappropriate mode switch episodes (stored in the IEGM memory) will undergo a far-field sensing test..

- Hereby intraatrial and intraventricular IEGM (atrial sensing amplification, Vtip-Vring), as well as extended marker and external ECG recordings of the pacemaker programmer are used
- Temporary programmed parametric settings
- Atrial sensing: 0.1 mV, bipolar
- PVAB 60 ms
- AV-time 70ms (ventricular pacing)

An ECG-stripe, recorded with 50 mm/s, has to be printed out. If there are black boxes (representing p-wave sensing within in the refractory period) the interval from the ventricular pacing marker to the P-marker (black box) has to be measured. This interval equals the coupling interval (CI) of the far-field R-wave signal.

The optimised PVAB will be programmed at CI +25ms, but not less than 85 ms.

The testing will be recorded with intrinsic conduction but also under pacing condition. In the course of the study a prolongation of the PVAB according to FFS test results is allowed. But there will be no shortening of the PVAB, only due to relevant clinical reasons.

#### 5.4.6 AV / PV Optimisation

The Choosing of an appropriate test in order to optimise AV / PV are left to each study centre.

### 5.5 Pacemaker programming guidelines

The following parametric settings represent the guidelines for the initial pacemaker programming and should be programmed. Not following the guidelines has to justified and documented..

- DDD- or DDDR-mode
- Atrial sensing: bipolar 0,3 mV
- PVAB within the study group: 60 ms / within the control group: based on the FFS-test (please see 5.4.5)
- AMS switched „on“ (DDIR) with setting the detection-threshold for atrial tachyarrhythmia at 180 min-1
- Triggering ECG-recording: AMS switched „on“; all others switched „off“
- Optimising the AV-time in order to enable a intrinsic conduction (via prolongation of the AV-time or via AV-hysteresis)
- Rate-adaptive AV-time: switched „off“

### 5.6 Adverse events (AE)

#### 5.6.1 Guidelines

A documentation of the event in terms of a detailed description, date and time of occurrence, length and course on the case report form is obligatory. Furthermore the event has to be classified in accordance to any association to the study procedure and in accordance to the degree of severity. The acute actions and the following medical treatments have to be documented as well.

Any patient, who face an adverse event, has to be monitored until the end of the event or its final evaluation. The occurrence of new symptoms or new secondary disorders, which have not be present at the inclusion, has also to be valued as an adverse event.

#### 5.6.2 Classification of adverse events

Any adverse event will be classified according to the below defined groups by the principle investigator, investigator or co-investigator. There will be a documentation of the rating on the case report form.

- **Class A:**Event, which is **associated** with a diagnostic assessment, an examination or medical, treatment according to the Avoid FFS study protocol.
- **Class B:**
- Event, which is **possibly associated** with a diagnostic assessment, an examination or medical, treatment according to the Avoid FFS study protocol
- **Class C:**
- Event, which is **not associated** with a diagnostic assessment, an examination or medical, treatment according to the Avoid FFS study protocol.
- **Class D:**Event, whose **association** to a diagnostic assessment, an examination or medical, treatment according to the Avoid FFS study protocol **cannot be evaluated**.

#### 5.6.3 Serious adverse events

All serious adverse events will be classified in according to the degree of severity.

##### 5.6.3.1 Mild adverse events

Events, which may only require basic medical treatment or basic diagnostic assessment and is usually transient

##### 5.6.3.2 Moderate adverse events

Events, which requires medical treatment or diagnostic assessment and is remediable or persist in a tolerable way

##### 5.6.3.3 Serious adverse events

Serious adverse events are any untoward medical occurrence that is life threatening or results in persistent or significant disability/incapacity. Furthermore any adverse events which possibly results in death, requires inpatient hospitalization or prolongation of existing hospitalization, causes congenital anomaly/birth defects or leads to permanent impairment or damage.

In case of serious adverse events the principle investigator, the sponsor and the ethics committee have to be informed immediatly abourt the occurrence.

#### 5.6.4 Reporting of adverse events

Table 1 illustrates the reporting lines and periods in case of adverse envents:

| **Class** | **Degree of severity** | **Who reports?** | **To whom?** | **Within** |
| --- | --- | --- | --- | --- |
| A, B, C, D | mild | Investigator | Sponsor | 3 working days |
| moderate |
| serious | Investigator | Sponsor,  Principle Investigator,  Ethics committee | 1 working day  Notification by phone in advance |

Table 1: Reporting and reporting lines in case of adverse events

#### 5.6.5 The course of an adverse event

The course of an adverse event will be evaluated along the following criteria at the end of the follow-up period or at the end of the event.

- The adverse event was transient.
- The adverse event is ongoing but persist in a tolerable way
- The adverse event led to a permanent impairment or damage
- The adverse event resulted in death.

### 5.7 Risks

All participants face the general risks associated with a pacemaker implantation and the possible complications in the long-term

**Additional study-related risks:**

none

### 5.8 Advantages

The new atrial lead Tendril 1699 has shown an reducing impact on the far-field R-wave amplitude. Consequently the PVAB can be kept short, which in turn goes along with an even improved atrial sensing. In particular the likelihood of 2:1 lock-in of atrial flutter could be lowered.

Furthermore as no more far-field sensing tests and no more individual adjustments of the PVAB are needed, the use of the lead leads to a time saving in follow-up visits.

## 6 Valid Implants

Within the Avoid FFS Study only CE-certified implants will be used.

Pacemaker: Identity ADx DR; Victory**TM** DR or follow up model

Atrial lead: Study group: Tendril 1699 / Control group: Tendril 1388, 1688 or 1788

Ventricular lead: CE-certified lead

## 7 Statistical consideration

### 7.1 Randomisation

The randomisation will be performed centre-stratified in groups of 4. Each participating centre will receive its own randomisation in 4 numbered, sealed envelopes. The master randomization list remains in the hand of St. Jude Medical GmbH, Eschborn.

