### 5.1 Study course

After giving a written informed consent for participating in the trial the patient will receive a dual chamber pacemaker according to the study protocol.

Prior to pacemaker implantation the patient will be randomly assigned to the study group with receiving a novel atrial lead with a short tip-to-ring distance (Tendril 1699) or to the control group with receiving a conventional atrial lead (Tendril 1388, 1688 or 1788)

In the study group the PVAB will be fixedly programmed at 60ms. Whereas in the control group the coupling interval will be defined according to a far-field sensing test and finally the optimized PVAB will be programmed at the coupling interval plus 25 ms. (see below: 5.4.5 far-field sensing test, as well as 5.5 pacemaker programming guidelines)

The primary endpoint will be the occurrence of an inappropriate mode switch due to FFS assessed by stored episodes of the pacemaker within the first 3 months after implantation.

In case of an inappropriate mode switch the far-field sensing test will also be applied to a patient of the study and the PVAB will be programmed at the coupling interval plus 25ms. The 3 months follow up of these patients will be continued.

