#### 5.4.2 Implantation and revision surgery

The patients will receive a licensed pacemaker (Identity ADX DR, XL DR, Victory DR or any dual chamber follow-up model produced by St Jude Medical) and according to randomisation a matching, bipol, CE-certified atrial lead (Tendril 1699 in the study group and Tendril 1388, 1688 or 1788 in the control group), as well as a CE-certified ventricular lead (see section 6).

An implantation form will be filled in for each operation. Even in case of revision surgery without device removal or change an implantation form will document the reasoning for revision.

The following implantation data will be recorded:

- Implantation date
- Device-type, device-id and serial number
- Atrial and ventricular sensing threshold (PSA / pacemaker)
- Atrial and ventricular pacing threshold and lead impedance (PSA / pacemaker)
- Atrial and ventricular signal amplitude (PSA / pacemaker)
- Atrial lead placement
- Adverse events / surgery related events

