**PHD**

- Follow-up date
- Current antiarrhythmic medication
- Pacemaker parameters (sensing and pacing thresholds, impedance of the leads etc)
- Keeping records of AF-burden-, mode-switch-, frequency- and sensor histogram, inclusive all stored IEGMs, and deleting the pacemaker storage afterwards
- Far-field sensing test within the control group only (please see 5.4.5)
- Programming according to the study guidelines (please see 5.5)
- Adverse events

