### 7.2 Statistical Methods

Details:

Power = 80%

Groups: 1388/1688/1788 lead vs 1699 lead

Endpoint: % of inappropriate MS due to FFS

When 75 patients are recruited in each group, the lower limit of the observed one-sided 95% confidence interval will be expected to exceed -10% with 80% power when the Standard (1388/1688/1788) proportion, is 5% and the Test (1699) expected proportion, pT, is also 5%; results are based on 1000 simulations using the Newcombe-Wilson score method to construct the confidence interval. (Newcombe RG (1988) Interval estimation for the difference between independent proportions: comparison of eleven methods. Statistics in Medicine 17:873-890.)

Hence, assuming a drop-out rate of 10% you need to recruit **168 patients**.

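### Constant blocks of 4 within centre, stated in the protocol of a trial whose arms are visible on site, let an enroller who keeps a tally know up to one third of assignments in advance

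*Protocol*

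**What the plan says.** Protocol section 7.1 sets the method in three sentences: "The randomisation will be performed centre-stratified in groups of 4"; "Each participating centre will receive its own randomisation in 4 numbered, sealed envelopes"; and "The master randomization list remains in the hand of St. Jude Medical GmbH, Eschborn". It describes no variation in block size and no step in which an assignment is released centrally for each patient. Since 4 envelopes make up one block, the text also leaves open how a centre receives its next block.

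Section 5.1 fixes the timing: "Prior to pacemaker implantation the patient will be randomly assigned to the study group" or to the control group. Section 7.2 implies 1:1 allocation: "When 75 patients are recruited in each group".

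The protocol never calls the trial open-label, but three provisions make the arm plain to site staff:

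- Section 5.4.2, the lead implanted: "Tendril 1699 in the study group and Tendril 1388, 1688 or 1788 in the control group".
- Section 5.4.3.1, the pre-discharge visit: "Far-field sensing test within the control group only (please see 5.4.5").
- Section 5.5, the programming: "PVAB within the study group: 60 ms / within the control group: based on the FFS-test".

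Under section 4.4, investigators and co-investigators both recruit patients and carry out the follow-up. They also submit this protocol for ethical review, so they know the block size.

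**The concern.** A sealed envelope hides the next assignment only as long as it cannot be worked out from earlier ones. With 1:1 blocks of constant and known size 4, the rest of a block is settled once two of its patients have gone to the same arm, and the fourth assignment is always settled. Stratifying by centre keeps the tally short and local.

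A person who knows the next assignment can enrol, defer or pass over a candidate because of it. Eligibility is broad (section 5.2), so there is room for choice. Section 3.2 lists ventricular pacing percentage among the factors whose influence on inappropriate mode switch is to be studied, and section 5.4.1 records the underlying bradycardia at enrolment, which may give the recruiter some idea of it. With few expected events, a small shift in case mix between arms could carry weight in the primary comparison.

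**Working it through.** **Inputs.** From section 7.1: block size 4, constant, within centre. From section 7.2: equal groups of 75, 5% expected in each arm, one-sided 95% Newcombe-Wilson interval, margin 10 percentage points, 80% power, 10% dropout, 168 patients. The 2+2 composition of a block is inferred from the equal groups.

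**The plan's own figures.** Section 7.2 reproduces. Exact enumeration at 75 per arm gives power 0.806 against the stated 0.80, and 75/(1 − 0.10) = 83.3, rounded up to 84 per arm, gives 168. The protocol gives no figure for predictability, so the rest is new calculation.

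**Certain assignments.** There are C(4,2) = 6 equally likely blocks.

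| Position in block | Probability that the assignment is already certain |
|---|---|
| 1 | 0 |
| 2 | 0 |
| 3 | 1/3 (the first two were alike) |
| 4 | 1 |

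The mean is (0 + 0 + 1/3 + 1)/4 = 1/3, which is 8 of the 24 positions. Applied to 168 patients this is 168/3 = 56, if every block is completed and the enroller tracks all earlier assignments.

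**Best guess.** Guessing the arm that is behind, and tossing a coin when the arms are level, is right in 17/24 = 70.8% of cases, against 50% by chance.

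**How few events decide the result.** Expected events are 2 × 75 × 0.05 = 7.5. Section 7.2 writes the criterion as a lower limit above −10%. Expressed as test minus control, this means an upper limit below 10%:

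U = (pT − pC) + √[(uT − pT)² + (pC − lC)²]

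Here uT is the Wilson upper limit for the test arm and lC the Wilson lower limit for control, both at one-sided 95% (z = 1.645). With 8 events and 75 per arm:

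| Test vs control events | pT − pC | uT | lC | U | Below 10%? |
|---|---|---|---|---|---|
| 4 vs 4 | 0.0000 | 0.1136 | 0.0242 | 6.7% | yes |
| 5 vs 3 | 0.0267 | 0.1307 | 0.0161 | 9.5% | yes |
| 6 vs 2 | 0.0533 | 0.1473 | 0.0089 | 12.3% | no |

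For 5 vs 3: 0.0267 + √(0.0640² + 0.0239²) = 0.0950. For 6 vs 2: 0.0533 + √(0.0673² + 0.0178²) = 0.1230. From 5 vs 3, one event changing arm reverses the conclusion; from 4 vs 4, two do.

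**Effect of the alternatives.** The same enumeration covers other constant, known sizes. For varying sizes I simulated centres of 8 to 40 patients, with an enroller who knows which sizes are possible but not their order.

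| Scheme | Certain in advance | Best guess right |
|---|---|---|
| Constant 2 | 50% | 75.0% |
| Constant 4 (the plan) | 33.3% | 70.8% |
| Constant 6 | 25% | 68.3% |
| Constant 8 | 20% | 66.6% |
| Random 4 and 6 | about 6% | about 67-69% |
| Random 4, 6 and 8 | about 2-3% | about 66-68% |

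**The case against.** Several points on the other side stand.

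- **This is a design choice, not an error or contradiction.** Small blocks protect balance in small centres, the envelopes are sealed and numbered, and the sponsor holds the master list. Section 5.1 already places consent before treatment and assignment before implantation. What is missing is an explicit rule on what must be recorded before an envelope is opened; section 5.4.1 merely lists randomisation as an item on the enrolment form.
- **One third is an upper bound.** Incomplete final blocks, or several enrollers who share no tally, lower it. The protocol does not say how many centres take part or how many patients each enrols, so the figure of 56 cannot be confirmed.
- **Varying the blocks barely reduces guessing.** To guess the arm that is behind, one needs only the centre's running imbalance, not the block size. The gain lies in removing certainty.
- **The link from foreknowledge to outcome is only partly documented.** Section 3.2 names ventricular pacing percentage as a factor to be examined, not an established cause, and section 5.5 asks for AV timing that favours intrinsic conduction in both arms.

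A reader might go further and infer that steering a few patients would overturn the result. The documents do not support that. The working counts events, and a steered patient is not an event. If steering changed a patient's risk by an assumed 5 to 25 percentage points, two net events would take about 2/0.25 = 8 to 2/0.05 = 40 steered patients. Nor does any passage tie a history of atrial arrhythmia to mode switch caused by far-field sensing, so that route should not be argued.

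**Conclusion.** The point holds as a cheap improvement. As written, section 7.1 lets an enroller who tracks the centre's assignments be certain of up to one third of them, at most about 56 of 168. This rests on 2+2 blocks, completed blocks, a shared tally, and envelopes being opened at the centre; the first and last are inferred from the text. The protocol shows an opening for selection bias. It does not show that anyone used it, or in which direction a bias would run. The opening is worth closing because, with about 7 to 8 expected events, the conclusion can turn on one or two. The sample size is unaffected.

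**What to change.** Amend section 7.1 as follows:

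- Keep stratification by centre, but generate each centre's list with randomly varying block sizes, for example 4 and 6, or 4, 6 and 8. Avoid 2, which is the most predictable size.
- Remove the block size from the protocol given to centres and keep it with the sponsor's master list.
- Supply each centre with one continuous numbered series of envelopes in place of sets of 4.
- State that an envelope is opened, in sequence, only after consent and eligibility have been recorded.

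Certain foreknowledge then falls from 33% to about 2-6%. The best-guess rate falls only to about 66-69%, so the change should not be presented as making assignments unpredictable.

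The cost is a new list from the sponsor and a few sentences in section 7.1. The downside is a slightly larger possible imbalance between arms within small centres.

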### 7.2 Statistical Methods

Details:

Power = 80%

Groups: 1388/1688/1788 lead vs 1699 lead

Endpoint: % of inappropriate MS due to FFS

When 75 patients are recruited in each group, the lower limit of the observed one-sided 95% confidence interval will be expected to exceed -10% with 80% power when the Standard (1388/1688/1788) proportion, is 5% and the Test (1699) expected proportion, pT, is also 5%; results are based on 1000 simulations using the Newcombe-Wilson score method to construct the confidence interval. (Newcombe RG (1988) Interval estimation for the difference between independent proportions: comparison of eleven methods. Statistics in Medicine 17:873-890.)

Hence, assuming a drop-out rate of 10% you need to recruit **168 patients**.

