## 1 Introduction

### 1.1 Current state of research

Far-field R-wave sensing (FFS) has been identified as the most common cause for inappropriate mode switch in dual chamber pacemakers.

Under default pacemaker settings and by using a conventional bipolar atrial lead the incidence of inappropriate mode switch is 20%-30%1/2. Applying a far-field R-wave sensing test and adjusting the post ventricular atrial blanking period (PVAB) can reduce the incidence of inappropriate mode switch to 10%3.

In recent studies a newly developed atrial lead with a short bipol distance has shown a relevant reduction on the far-field R-wave amplitude whereas the amplitude of the near field signal (p-wave) remains comparable to conventional leads.

The aim of the study is to show, that using an atrial lead with a very short tip-to-ring spacing can avoid inappropriate mode switch with neither any additional testing nor any individual adjustments of pacemaker settings (Sensing, PVAB)

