## 2 Hypothesis given

The new atrial lead Tendril 1699 with a short tip-to-ring distance goes along with a reducing impact on the far-field R-wave amplitude and consequently avoids inappropriate mode switch. Thus by using the new leads with a short bipol spacing there is no need for additional far-field sensing tests and for individual adjustments of pacemaker settings

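### Section 7.2 plans on a 5% control incidence without a source, while section 1.1 gives 10% for the same strategy; with both arms at 10%, power is about 63% rather than 80%

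*Protocol*

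**What the plan says.** **Sample size (Protocol 7.2).** The design is a non-inferiority comparison: "the lower limit of the observed one-sided 95% confidence interval will be expected to exceed -10% with 80% power". The planning rates apply "when the Standard (1388/1688/1788) proportion, is 5% and the Test (1699) expected proportion, pT, is also 5" (per cent), with 75 patients per group and a Newcombe-Wilson score interval. Allowing for 10% dropout gives 168 patients. No source or reason accompanies the 5% or the margin.

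**Background (Protocol 1.1).** For a conventional bipolar lead at default settings, "the incidence of inappropriate mode switch is 20%-30%1/2". Running an FFS test and adjusting the PVAB "can reduce the incidence of inappropriate mode switch to 10%3". The digits after the percentages are reference numbers.

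**Control arm (Protocol 3.1 and 5.1).** Control patients receive a conventional lead, with the PVAB set individually from the FFS test. This is the strategy to which section 1.1 attaches the 10%.

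**Hypothesis (Protocol 2).** With the new lead, "there is no need for additional far-field sensing tests and for individual adjustments of pacemaker settings".

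**The concern.** The only incidence that the protocol gives for the control strategy is twice the rate used to size the trial, and nothing explains the gap. This matters because, with a fixed absolute margin, the variance of the difference grows as the rates rise from 5% towards 10%, and power falls. If both strategies truly ran at 10%, the trial would miss its criterion more than one time in three although the lead was no worse.

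The same background figures bear on the margin. They imply a benefit of the control strategy over default settings, and a non-inferiority margin is normally judged against that benefit. The protocol does not make the comparison.

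**Working it through.** **Inputs.** From section 7.2: 75 evaluable per group, 10-point margin, one-sided 95% limit (z = 1.645), Newcombe-Wilson method. From sections 7.2 and 1.1: control incidence 5% and 10% respectively. Rates of 6% to 8% are intermediate values chosen to show the range.

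**Method.** For x_T events on the new lead and x_C on control, let p = x/n. The Wilson limits l and u for each arm are

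(2np + z² ± z·√(z² + 4np(1 − p))) / (2(n + z²)).

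The upper limit for the excess on the new lead is

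U = (p_T − p_C) + √[(u_T − p_T)² + (p_C − l_C)²].

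The trial succeeds if U < 10 points. This is the protocol's criterion with the sign turned round; at equal rates both readings give the same power. Power is the sum of the binomial probabilities over all pairs (x_T, x_C) that succeed, which replaces the protocol's 1000 simulations with an exact figure.

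**One pair worked through.** With 7 events in each arm, p = 7/75 = 9.33%, l = 5.14%, u = 16.36%. Then U = 0 + √(7.03² + 4.19²) = √(49.4 + 17.6) = 8.2 points, a success.

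**Reproducing the plan.** At 5%/5% and 75 per group, exact power is 80.6%, which agrees with the stated 80%. Dropout: 75/0.9 = 83.3, so 84 per group and 168 in total, also as stated.

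**Changing the rate, keeping the plan's equal-rates assumption (75 per group)**

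| Control and test rate | Power |
|---|---|
| 5% | 80.6% |
| 6% | 76.0% |
| 7% | 72.0% |
| 8% | 68.6% |
| 10% | 62.8% |

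If all 84 recruited per group were evaluable, power at 10%/10% would be 67.6%. Reaching 80% at 10%/10% would take about 117 evaluable per group; 117/0.9 = 130 per group, or 260 in total.

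**Changing only the control rate, to 10% (75 per group)**

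| Test rate | Power |
|---|---|
| 5% | 95.9% |
| 6% | 92.0% |
| 7% | 86.5% |
| 8% | 79.6% |
| 10% | 62.8% |

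**Margin against the benefit in section 1.1.** Low end: 20% − 10% = 10 points, and 10/10 = 100%. High end: 30% − 10% = 20 points, and 10/20 = 50%. The margin is therefore half to all of the implied benefit.

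**The case against.** **The calculation is not wrong.** A reader might infer that the stated 80% is an arithmetic error and that the true power is 63%. The documents do not support that. The 80% is stated conditionally on 5% in both arms and reproduces under that condition, as does 168.

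**The 63% needs the new lead to run at 10% as well.** No section says so. Section 1.1 attaches 10% to the control strategy, and sections 1.1 and 2 expect the new lead to do well. With control at 10% and the new lead at 5%, power is 96%. This stands, and the unequal cases belong beside the equal ones. It does not remove the point: section 7.2 itself plans on equal rates, so putting the protocol's own control figure into that design is the like-for-like check. A plan that relied on the new lead being better would have to say so.

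**The two rates may not measure the same thing.** Section 1.1 speaks of inappropriate mode switch, states no follow-up period, and calls FFS the most common cause, not the only one. Sections 5.1 and 7.2 count FFS-caused episodes, over 3 months. A rate below 10% is plausible, so the difference is unexplained rather than a proven contradiction. The protocol does not make this argument, and even at 7% to 8% in both arms power is 72% to 69%.

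**The margin can be overstated in two ways.** A reader might infer that it equals the control strategy's whole benefit; that holds only against the 20% end of the background range. A reader might also infer that a pass would show no more than superiority to default settings. That confuses the null boundary with the evidence. With 75 per group a pass needs nearly equal counts: at most 5 test events against 4 control events, or at most 8 against 7. True rates of 5% against 15%, or 10% against 20%, would pass only about 5% of the time.

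**Conclusion.** The point holds as an unsupported planning assumption on which the stated power and the 168 patients rest. Under the plan's own equal-rates assumption, power falls from 80.6% at 5% to 62.8% at the 10% of section 1.1, a loss of 80.6 − 62.8 = 17.8 points. If the control rate is 10%, power of about 80% or more requires a true rate on the new lead of about 8% or lower. These figures assume 75 evaluable per group, the 10-point margin and the one-sided 95% Newcombe-Wilson limit without continuity correction.

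The margin, at 50% to 100% of the benefit implied by section 1.1, has no stated rationale. That comparison assumes the background figures carry over to this trial's endpoint and follow-up, which the protocol does not establish.

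Section 2 states a hypothesis, not a success criterion, so its wording is not itself an error. What a positive result can support is non-inferiority within 10 percentage points.

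**What to change.** Keep the sample size and reconcile section 7.2 with section 1.1 in one of two ways:

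- state why 5% applies to FFS-caused episodes over 3 months in the control arm, with its source; or
- restate the power for 75 evaluable patients per group as about 81% at 5%/5%, 72% at 7%/7% and 63% at 10%/10%, and add that with control at 10% it runs from 96% (test 5%) to 80% (test 8%).

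In either case, give the reason for the 10-point margin in light of the 10 to 20 point benefit in section 1.1, and state that a positive result will be reported as non-inferiority within 10 percentage points.

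The cost is wording in section 7.2 and, under the second option, a less favourable stated power. No extra patients or changes to conduct are needed.
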